### Inclusion and exclusion criteria

We include adults aged 18 – 65 years with one or more of the following DSM-IV diagnoses: major depression (single episode or recurrent), dysthymia, panic disorder (with or without agoraphobia), social phobia or generalized anxiety disorder, including comorbid diagnoses. We also include patients with a minor depression or a minor anxiety disorder. We use the DSM-IV research criteria to define minor depression. The main difference between the criteria of minor and major depression is that for minor depression only two to four out of nine symptoms have to be present, of which at least one has to be a core symptom (depressed mood or markedly diminished interest or pleasure in all, or almost all, activities). As there are no DSM criteria, we define a minor anxiety disorder as a score of 12 or more on the Hospital Anxiety and Depression Scale [31] and dysfunctioning in daily life (household, work and/or social relations). Exclusion criteria are psychotic or bipolar disorder, current (< 2 months) treatment (medical/psychotherapy) for psychological problems, prominent suicide ideation, severe alcohol problems (> 20 on the Alcohol Use Disorders Identification Test (AUDIT)[32], no motivation for treatment and insufficient knowledge of the Dutch language.

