#### Recruitment of patients

Patients are recruited by screening all patients of the participating GPs during the inclusion period of 1,5 year. All patients with a positive screen for depression and/or anxiety are assigned to a watchful waiting period of 4 weeks. After 4 weeks every patient is screened again to exclude the patients who recover spontaneously. This second screener is the baseline questionnaire (T0) and is sent to each patient together with general information about the project and an informed consent form. Two weeks later the patients are approached for a diagnostic interview (Composite International Diagnostic Interview: CIDI) [33] by telephone to check for in- and exclusion criteria. Patients who meet the inclusion criteria *and *return their informed consent are randomised.

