### Randomisation

Randomisation takes place at an individual level. Patients are randomised into two groups, stratifying by care manager and using blocks of 4 to prevent overburdening the care managers. An independent researcher not involved in the current project uses computer generated block randomisation to produce sealed envelops. After every inclusion the researcher opens a sealed envelop.

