### Sample Size

A meta-analysis on the effects of psychological treatment on patients with sub-clinical depression shows an effect size of 0.40. Based on a power of 0.80 in a two-tailed test and an alpha of 0.05, we need 100 patients in each condition. Therefore, the total sample size is set at 200.

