### Statistical Analysis

All analyses will be conducted according to the intention-to-treat principle. All respondents who have been randomised will be included in the analyses examining the effects of the intervention. Missing data will be imputed using regression imputation. The effectiveness of the stepped care program is measured via the primary outcomes: the HADS (anxiety) and IDS (depression). It is useful to know not only wether the effectiveness is statistically significant, We will use Cohens' *d *[71] to measure the size of the effect. Furthermore, GEE-analysis will be used to examine differences in speed of recovery between the two groups [72]. Additionally, we will report the percentage of patients who have recovered at the moment of the last assessment. In order to do so we will calculate the relative risk.

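### The analysis section does not say that the IDS and HADS-A comparisons adjust for the T0 score or for care manager; unadjusted, they would be valid but would give up available precision

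*Protocol article*

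**What the plan says.** All places are in the protocol article.

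- **Randomisation:** "Patients are randomised into two groups, stratifying by care manager and using blocks of 4 to prevent overburdening the care managers".
- **Recruitment of patients:** "This second screener is the baseline questionnaire (T0) and is sent to each patient together with general information about the project and an informed consent". The diagnostic interview and randomisation come later, so T0 is a pre-randomisation measurement.
- **Table 1:** IDS and HADS-A are scheduled at T0, T1, T2 and T3.
- **Inclusion and exclusion criteria:** besides several full DSM-IV mood and anxiety diagnoses, "We also include patients with a minor depression or a minor anxiety disorder".
- **Sample Size:** "A meta-analysis on the effects of psychological treatment on patients with sub-clinical depression shows an effect size of 0.40". Then: "Based on a power of 0.80 in a two-tailed test and an alpha of 0.05, we need 100 patients in each condition". No covariate enters this calculation.
- **Statistical Analysis:** the section names intention to treat, regression imputation, HADS and IDS as primary outcomes, Cohen's d as the effect size, a relative risk for recovery at the last assessment, and one longitudinal method: "GEE-analysis will be used to examine differences in speed of recovery between the two groups". It lists no covariates for any of these, does not say which time points form the GEE outcome, and does not name the predictors in the imputation.

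**The concern.** The two primary outcomes are measured before randomisation, yet the section that says how the effect is estimated does not mention using those measurements. In this trial they should be informative. The sample mixes minor and major depression, dysthymia and several anxiety disorders. A patient with anxiety only may score low on IDS, and one with depression only may score low on HADS-A, so a wide T0 spread on each outcome is to be expected. Severity is not a stratification factor, so the design does not balance it.

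Two things are at stake. The first is precision on both primary outcomes, which can be had from data already scheduled. The second is pre-specification: with two primary outcomes, it should be settled before the data are seen whether the reported effect is baseline-adjusted. Otherwise adjusted and unadjusted results are both available to choose from.

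Care manager is a lesser matter of the same kind. The design forms strata by care manager, and the analysis section does not say that the strata are carried into the comparison.

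**Working it through.** **Inputs from the article.** d = 0.40, so SD = 1 on the standardised scale; two-sided alpha 0.05; target power 0.80; 100 per arm (Sample Size).

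**Inputs not in the article, assumed.** Correlation r between the T0 and T3 score of the same outcome: 0.3 to 0.6. Share of outcome variance lying between care managers (ICC): 0.01 to 0.10. No dropout is applied.

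**1. Reproduce the planned size.** Normal approximation: n per arm = 2 × (1.960 + 0.842)² / 0.40² = 98.1, rounded up to 99. The two-sample t calculation gives 99.08, rounded up to 100. Power of the two-sample t-test at 100 per arm is 0.804. The stated figure is correct and takes no credit for baseline adjustment.

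**2. Adjust for T0.** A linear adjustment multiplies the residual variance by 1 − r². The standardised effect becomes 0.40 / √(1 − r²), and the equivalent unadjusted size is 100 / (1 − r²). Power is from the two-sample t-test at 100 per arm.

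| r (assumed) | 1 − r² | effect / residual SD | equivalent n per arm | power |
|---|---|---|---|---|
| 0 (unadjusted) | 1.00 | 0.400 | 100 | 0.804 |
| 0.3 | 0.91 | 0.419 | 110 | 0.839 |
| 0.4 | 0.84 | 0.436 | 119 | 0.867 |
| 0.5 | 0.75 | 0.462 | 133 | 0.901 |
| 0.6 | 0.64 | 0.500 | 156 | 0.940 |

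**3. Adjust for care manager only.** With strata balanced by design, the residual variance is multiplied by 1 − ICC.

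| ICC (assumed) | effect / residual SD | power |
|---|---|---|
| 0.01 | 0.402 | 0.808 |
| 0.05 | 0.410 | 0.823 |
| 0.10 | 0.422 | 0.843 |

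The gain is small throughout. Leaving out the strata tends to make the standard error too large, which is the conservative direction.

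**4. Size of chance imbalance.** The standard error of the T0 difference between arms is √(2/100) = 0.141 SD. With r = 0.5 and equal SDs at T0 and T3, a two-standard-error imbalance moves an unadjusted difference in follow-up scores by 2 × 0.141 × 0.5 = 0.14, about a third of the design effect of 0.40. This is random error, which the unadjusted standard error already covers. It is not bias. Adjustment removes it from the estimate.

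**The case against.** The strongest reply is that silence is not exclusion. The section nowhere says that the analyses are unadjusted. A GEE on speed of recovery may well carry T0 as its first repeated measure or as a covariate, the imputation may use it, and d could come from change scores or from a model. The article is condensed, and covariate lists are often left to an analysis plan that is not shown. This stands against any claim that the trial discards its baseline data, and a reader tempted to infer that should not.

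It does not dispose of the point. The article assigns the GEE to speed of recovery and the size of the effect to Cohen's d. A GEE that includes T0 would not by itself make that d adjusted. The only sizing calculation in the article is an unadjusted two-group one.

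Three further objections stand:

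- A reader might infer that planned power is lost. It is not: 100 per arm gives 0.804 without adjustment, before any dropout. What is at issue is precision forgone, not a shortfall.
- A reader might infer that ignoring the strata invalidates the standard errors. The error is conservative, and the article gives a workload reason for the blocking, "stratifying by care manager and using blocks of 4 to prevent overburdening the care managers", not a claim that care manager is prognostic.
- The gains depend on a correlation that the article does not report.

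**Conclusion.** The point holds as a matter of precision and pre-specification, not validity. The article describes the effect on IDS and HADS without stating any adjustment for the T0 score of that outcome or for care manager. The sample size is right, and an unadjusted analysis would be valid.

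If r lies between 0.3 and 0.6, adjusting for T0 cuts the residual variance by 9% to 36% and raises power at d = 0.40 from 0.80 to 0.84–0.94. The care-manager term is worth little in power (0.81–0.84 for an ICC of 0.01–0.10); its main use is to match the standard error to the randomisation. These figures describe a comparison at one time point with complete data, and both r and the ICC are assumptions.

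The gap does not by itself dictate a particular primary time point, a particular SD for d, or an adjusted relative risk. Those are separate choices.

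**What to change.** Add one sentence to Statistical Analysis: the between-group comparisons of IDS and HADS-A, and the Cohen's d derived from them, are adjusted for the T0 value of that outcome and for care manager. If an unpublished analysis plan already says this, it is enough to repeat it in the article's analysis section.

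The cost is the sentence itself. T0 scores are already scheduled in Table 1, and care manager is recorded as the randomisation stratum. The sample size of 200 need not change.

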## Discussion

This paper describes the design of a study to investigate the effectiveness of stepped care for patients with minor and/or major depressive and anxiety disorders in comparison with care as usual in general practice. The following four steps are included in the stepped care model: watchful waiting, guided self-help, PST and pharmacotherapy and/or referral to mental health care. All these interventions are evidence based but there is a lack of studies regarding the effectiveness of stepped care as a whole. Results of this study could offer encouragement for the implementation of an effective stepped care model.

A major strength of this study is that it is a pragmatic randomised trial. In a pragmatic trial, patients and therapists are the same as those seen in daily practice. This means that the sample of patients may be quite heterogeneous (may have mild to severe depression/anxiety with or without psychiatric or somatic co-morbidity) and that the therapists (psychiatric nurses or psychologists) have average qualifications (instead of top level therapists from an academic centre). This enhances external validity which means that the results of this study will reflect the 'real' effects of daily practice. If an intervention is shown to have a significant beneficial effect in a pragmatic trial then it has been shown not only that it can work, but also does work in real life [73].

This advantage of the study has also some risks. First of all, it is difficult to maintain treatment integrity when conducting a study in day-to-day clinical practice and using personell not specifically hired for research. We hope to minimize this limitation by organizing strict supervision of the care managers.

Secondly, it is possible that there is a bias in our GP recruitment. To conduct this study, we need GPs who work together with a psychiatric nurse. This could mean that these particular GPs are aimed at mental health problems more than their colleagues who work without psychiatric nurse in their practice. If the GPs in our study pay more attention to mental health problems then GPs without psychiatric nurses, then our care as usual might be more adequate then care as usual in general.

Another limitation of our study could be the fact that we choose to recruit people with a diagnosis who do not receive any form of care and/or medication. There is a possibility that these patients have visited the GP before, but were not recognized as mental health patients. These patients might differ in a number of aspects from those who were recognized as mental health patients by their GP. It is possible that this leads to selection bias. To examine this we will conduct a non-response research.

It is widely acknowledged that depression recognition and management in primary care can be improved. As a consequence many collaborative care models, or disease management strategies, have been developed in recent years. The core elements of these care models are (1) an enhanced case management role for nonmedical specialists such as practice nurses and (2) integrated working relationships between primary care and specialist/secondary services [74]. In general these models seem to improve depression treatment [75]. Previous research into a partly implemented stepped care model in secondary services has shown cost-effectiveness compared to care as usual [29,76]. However, to our knowledge, our trial is the first trial with a fully implemented stepped care model for depression and anxiety treatment in primary care compared to care as usual.
